### Objectives and hypotheses

The study will address the following specific objectives:

Clinical outcomes: assess the impact of the complex intervention on ICU LOS, the duration of mechanical ventilation and other organ replacement interventions and the proportion of patients with limitations of life-sustaining therapies.Quality of life: assess the impact of the intervention on health-related quality of life (HRQoL).Economic evaluation: estimate impact on resource use, analyse cost implications and determine the cost-effectiveness and cost–consequence situation of the intervention.Perception of care: evaluate whether patients and their relatives experience improved care quality and communication in the ICU, particularly in relation to end-of-life care and symptom management.Staff well-being: examine whether ICU clinicians (both physicians and nurses) report fewer stressors and perceive an improved ethical decision-making climate and practice.

The primary hypothesis is that the complex intervention will reduce the average ICU LOS by at least 2 days compared with standard care before. Secondary hypotheses include an increase in treatment limitation decisions; improved economic efficiency; enhanced perceived quality of care (notably in symptom management and shared decision-making); an improvement in HRQoL among survivors; and ameliorated moral distress among ICU clinicians.

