## Methods

### Overview

We intend to complete a controlled, cluster-randomised, non-blinded stepped-wedge design trial with crossover phase to compare the intervention with standard treatment. Each cluster is formed by all participating ICUs sharing staff within one building or healthcare institution. Standard treatment is provided during the observation phase and the intervention is delivered during the subsequent intervention phase. All ICUs start with the observation phase. All patients who fulfil the eligibility criteria, including the ICU physician’s assessment of the need for specialised PC, are asked to participate in the study. At a randomised time point, each ICU cluster enters a crossover period of 1 month (see online supplemental material figure 1). Within this month, ICU staff receive online training in basic PC and EPIC interventionists are trained to conduct telepalliative consultations. In the subsequent intervention phase, the ICU physicians can use a newly developed checklist to assess specialised PC needs and schedule at least one specialised PC consultation via telemedicine. Survivors’ and relatives’ outcomes are gathered at pre-specified time points, that is, on ICU/hospital discharge and during a 3-month follow-up interview. Clinician outcomes (concerning burnout, end-of-life practices and ethical decision-making) are collected through a dedicated survey scheduled repeatedly in the control and intervention periods. The trial design is illustrated in figure 1.

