### Crossover phase: clinician education, bedside tools and interventionist training

In the crossover month, the Interdisciplinary Center for Palliative Medicine of the University Hospital Duesseldorf, Germany, provides a structured training programme to the physicians and nurses in the respective satellite ICUs (programme description available at https://clinicaltrials.gov/study/NCT06425692?term=enhancing-palliative-care-&rank=2). Training in PC is carried out online in a blended learning format^29^ with an interactive e-learning course and interactive webinars.^30^ Training impact is assessed by comparative self-assessment^31^ to assess predefined learning gains, and by the continuing professional response questionnaire,^32^ a validated tool to identify behavioural change. Training participation rate is determined as the ratio of the actual number of participants to the total number of eligible staff members of the participating ICUs.

Additionally, a newly developed checklist of possible trigger factors (box 1) is provided to the ICU staff to raise awareness for PC needs of ICU patients and their families daily and guide the tele-PC consultations. The checklist is based on literature research and developed by the Delphi process among participating clinicians of the EPIC consortium. An additional bedside tool is a factsheet with recommended PC practices and relevant legislation developed for this study by the department of intensive care medicine of the National and Kapodistrian University of Athens, Greece.

Box 1Trigger checklist for palliative care needs for intensive care unit patients and their familiesFrequent hospitalisations/emergency department visitsPersistent/uncontrolled symptomsExplore patients’ values and preferences and align the careAssistance with ascertaining goals of care or end-of-life planningPatient/family request for palliative care involvementExistential distress or spiritual concerns

The EPIC interventionists (PC consultants) in each hub who provide the teleconsultation have received a variable range of PC education and therefore will receive structured training to ensure a standardised approach according to current standards^25^ (box 2). Training impact is assessed by pretraining and post-training evaluations, using feedback surveys. Intervention fidelity is assessed by periodic (quarterly) audits of consultations, adherence to the protocol and clinician self-reports as described in further detail below.

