Cost-effectiveness, cost–consequence situation	Economic evaluation putting cost data in relation to patient and family outcomes.	Up to 3 months after hospital discharge

ICU, intensive care unit.

**Table 7 T7:** Clinician-related outcome measures*

Outcome measure	Measure description	Time frame
Burnout assessment	BAT-12 Short version, 12 questions	Up to 34 months
Inappropriate therapy	Perception of inappropriate therapy, 5 questions, answer format 5-point Likert scale (ranging from ‘never’ agree to ‘very often’)	Up to 34 months
Moral distress	Moral distress is measured per employee using a (0–10) numeric rating scale	Up to 34 months
End-of-life practice	12 questions regarding the current implementation of end-of-life practice, yes–no answer format	Up to 34 months
Ethical decision-making climate in the ICU	8 items, answer format 5-point Likert scale (ranging from ‘strongly agree’ to ‘strongly disagree’)	Up to 34 months
Existence of standard operating procedures	4 questions about the presence of written ICU protocols, yes–no answer format	Up to 34 months
Use of the ABCDEF bundle	11 questions, yes–no answer format	Up to 34 months
Supporting measures for patient/family	4 relevant questions, yes–no answer format	Up to 34 months
Perception of palliative care and law	4 relevant questions, yes–no–don’t know answer format	Up to 34 months
Barriers to palliative care	A multiple choice question	Up to 34 months
Facilitators for palliative care	A multiple choice question	Up to 34 months
Facilitators and barriers for provision of palliative and end-of-life care through telemedicine consultations in the ICU	Three open-ended questions	Up to 34 months

* Clinician outcome data are collected via an electronic questionnaire repeatedly throughout the observation and intervention periods.

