#### Data analysis plan

A detailed Statistical Analysis Plan will be finalised before database lock. The analysis of the data will begin with a detailed statistical description of the study sample, differentiated by control and intervention phase. Categorical characteristics will be summarised using absolute and relative frequencies. For ordinal or metric non-normally distributed data with up to five categories, we will present the absolute and relative frequencies, along with the median and the IQR. For data with more than five categories, only the median and IQR will be reported. For metric data that follows a normal distribution, we will present the mean value, accompanied by the SD and the 95% CI.

All analyses will be conducted on an intention-to-treat basis, with the patient representing the unit of analysis. We will use generalised linear mixed models (GLMMs) for continuous outcomes,^23 35^ accounting for the clustered data structure, to compare the primary endpoint between the control and intervention phases. Sensitivity analyses will include additional adjustment for ICU mortality.

Predefined subgroup analyses will be conducted to explore the heterogeneity of the treatment effect in patients concerning sex, religiosity, socioeconomic parameters and educational level. In addition, treatment effects will be compared between ICUs with high-tech versus low-tech telemedicine consultations, with good versus average or poor ethical climate, and ICUs with and without pre-existing palliative counselling. Further comparisons will be made among participating countries, patients with an ICU stay at enrolment of less than 5 days versus at least 5 days, and patients with versus without decisions to limit treatment at enrolment.

Subgroup analyses and analyses of all secondary endpoints will be considered as exploratory. Statistical testing will be carried out at a two-sided significance level of 5%. For the primary hypothesis, no correction for multiple testing is necessary.

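### Two subgroup splits taken at enrolment follow staff training and the checklist, so strata can shift by phase; ethical climate shares this only if classified after crossover

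*Protocol article*

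**What the plan says.** The Data analysis plan lists subgroup analyses meant to explore heterogeneity of the treatment effect. Three of them matter here:

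- ICUs "with good versus average or poor ethical climate", with no statement of which survey defines the class;
- "patients with an ICU stay at enrolment of less than 5 days versus at least 5 days";
- "patients with versus without decisions to limit treatment at enrolment".

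The same section labels all subgroup analyses exploratory.

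Other sections bear on when these variables arise:

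- **Training.** The Overview places staff education in the crossover month: "Within this month, ICU staff receive online training in basic PC".
- **Checklist.** The Crossover phase section says it is there to "raise awareness for PC needs of ICU patients and their families daily". The Discussion describes it as a tool for recognising need early.
- **Enrolment day.** Table 8 allows inclusion at any point once 72 hours have passed, with the teleconsultation within 48 hours after inclusion. Eligibility rests on the attending physician's judgement of need.
- **Limitation decisions.** Objectives and hypotheses states: "Secondary hypotheses include an increase in treatment limitation decisions".
- **Ethical climate.** An objective is that clinicians "perceive an improved ethical decision-making climate and practice". It is an outcome in Table 7, whose footnote says: "Clinician outcome data are collected via an electronic questionnaire repeatedly throughout the observation and intervention periods".

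**The concern.** A subgroup variable can show effect modification only if the intervention cannot change it. Here the intervention is a cluster-level package, and part of it (training and the checklist) is in place before any intervention-phase patient is enrolled. A value taken at enrolment therefore precedes the teleconsultation but follows exposure to the rest of the package.

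If the package works as intended, need is recognised sooner and limitations are discussed sooner. A patient who would have been enrolled on day 6 under control may be enrolled on day 4 under intervention. A patient without a limitation decision at enrolment under control may have one under intervention. The early and late strata, and the limited and unlimited strata, then hold different kinds of patients in the two phases. A difference in mean ICU stay between phases within a stratum mixes any treatment effect with this change of membership.

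At stake is the reading of these contrasts. A difference in apparent effect between early- and late-enrolled patients could be reported as heterogeneity when it reflects who was placed in which stratum. The exploratory label limits the strength of the claim; it does not remove the bias.

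**Working it through.** The protocol gives no figure for these subgroups, so there is none to reproduce. The check has two parts.

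**1. Order of events in the intervention phase**

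| Step | Place in the protocol |
|---|---|
| Staff training and checklist delivered | Overview; Crossover phase |
| Checklist in daily use by ICU staff | Crossover phase |
| Enrolment: ICU stay and limitation status fixed | Table 8, any time after 72 hours |
| Teleconsultation | Table 8, within 48 hours after inclusion |

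In the control phase the first two steps are absent. Each phase enrols different patients, so an intervention-phase patient has no pre-exposure value of either variable.

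**2. Size with no true effect**

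From the Sample size calculation: mean ICU stay 9 days, SD 9, intracluster correlation 0.01, target difference 2 days. The size of the shifts and the correlations are assumptions, because the protocol gives none. Effect means intervention minus control; contrast means the later stratum minus the earlier one.

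*Enrolment day, model A: recognition comes sooner, and only patients still in the ICU are enrolled.* Stay is 3 days plus a lognormal, giving total mean 9 and SD 9. The delay after 72 hours is exponential.

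| Mean delay, control to intervention | Effect, under 5 d | Effect, 5 d or more | Contrast | Unstratified |
|---|---|---|---|---|
| 4 to 2 d | -0.1 | -1.4 | about -1.3 | -1.2 |
| 3 to 1.5 d | -0.1 | -1.2 | about -1.1 | -1.05 |
| 3 to 2.5 d | -0.03 | -0.35 | about -0.3 | not zero either |

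Earlier recognition brings in shorter-stay patients who would otherwise have left unrecognised. In the first row the share enrolled rises from 57% to 74%, so the unstratified comparison is false as well.

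*Enrolment day, model B: the same patients in both phases, enrolled earlier in their stay.* Stay is 3 days plus a gamma with the same mean and SD. The enrolment day is set by the fraction of the post-72-hour stay already elapsed.

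| Mean fraction elapsed | Effect, under 5 d | Effect, 5 d or more | Contrast |
|---|---|---|---|
| 0.5 to 0.4 | +0.24 | +1.00 | 1.00 - 0.24 = +0.76 |
| 0.5 to 0.3 | +0.59 | +2.51 | 2.51 - 0.59 = +1.92 |

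Here the shorter stayers leave the late stratum and lengthen the early one, while the unstratified difference stays at zero. Other same-patient runs gave +0.4 to +0.9 and +1.4 to +3.5 days, so a contrast of up to 3.5 - 0.9 = 2.6 days. Models A and B give opposite signs.

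*Limitation at enrolment.* Assume a latent variable correlated ρ with stay, and a share with a limitation rising from p0 to p1. With z the upper-p normal quantile and φ the normal density, the false effects are:

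- with limitation: 9ρ[φ(z1)/p1 - φ(z0)/p0]
- without limitation: 9ρ[-φ(z1)/(1 - p1) + φ(z0)/(1 - p0)]

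For ρ = 0.3 (the signs reverse for ρ = -0.3):

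- 30% to 40%: with, 2.7 × (0.966 - 1.159) = -0.52; without, 2.7 × (-0.644 + 0.497) = -0.40; contrast size 0.12.
- 30% to 50%: with, 2.7 × (0.798 - 1.159) = -0.97; without, 2.7 × (-0.798 + 0.497) = -0.81; contrast size 0.16.

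*Ethical climate.* The between-cluster SD is 9 × √0.01 = 0.9 days.

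- If ICUs are reclassified by phase and the share rated good rises from 40% to 60-80%, the false within-stratum effects are about 0.1 to 0.7 days and the false contrast about 0.1 day at most.
- If each of 23 ICUs is classified once from a post-crossover survey, and ICU effects vary with SD 1 day and correlate 0.5 with climate improvement, a spurious 0.35 to 0.55 day difference appears.
- A pre-crossover survey gives none.

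**The case against.** Four objections have force.

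- **Climate.** A reader might infer that the plan forms the climate strata after crossover. It does not say so. It classifies ICUs and names no survey. Clinicians are also surveyed in the observation phase, so a sound classification is available, and the analysis plan not shown here may specify it. For climate the point is conditional.
- **Direction and cause.** A reader might infer that the trial would wrongly report more benefit in late-enrolled patients. That is one possibility: model A gives it and model B gives the reverse. In model A most of the distortion is differential enrolment, which also moves the unstratified comparison by about -1.2 days. Charging the whole -1.4 days to the subgroup split would be wrong.
- **Limitation.** The contrast between strata is hardly distorted (0.1 to 0.2 days). What suffers is the effect quoted within each stratum.
- **Remedy.** Deleting the splits would be more than is needed. Whether benefit depends on when need is recognised is a fair clinical question that admission diagnosis or severity cannot answer, and the enrolment-day distribution is a useful sign of shifted enrolment.

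The exploratory label lowers the stakes but does not answer the point. Nor is this merely a detail left to the analysis plan: the protocol itself fixes the two patient-level splits at enrolment, and an analysis plan that follows it inherits the problem.

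**Conclusion.** The point holds for ICU stay at enrolment and for limitation at enrolment, and conditionally for ethical climate. By the protocol's own account, both enrolment variables are recorded after part of the package has acted and in directions the package is meant to move, so stratum membership can differ by phase.

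Under the assumed shifts, the enrolment-day split can produce a false contrast of roughly 0.3 to 2.6 days, against a target effect of 2 days. Neither sign nor size is established. For limitation, the false within-stratum effects are about 0.4 to 1.0 days. For climate there is no problem if ICUs are classified before crossover. All these sizes would vanish if training and checklist did not change enrolment timing, limitation decisions or climate.

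Nothing here shows that the primary analysis is wrong: differential enrolment is a separate matter, and the choice of subgroups does not alter the primary test. Since the analyses are exploratory, the severity is minor.

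**What to change.** In the Data analysis plan, or in the statistical analysis plan before database lock:

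1. State that ethical climate is classified once per ICU, from its last observation-phase survey.
2. Report the distribution of ICU stay at enrolment and of limitation at enrolment by phase.
3. Keep these two splits, but present them as descriptive and conditional on post-exposure variables, not as evidence of effect modification.
4. Add effect-modifier subgroups fixed at ICU admission and already collected: admission severity score, admission diagnosis and pre-existing conditions.

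Step 4 prevents migration between strata. It does not correct any difference between phases in who is enrolled.

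The cost is wording only, with no new data. The downside is that two planned contrasts lose their causal interpretation.

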#### Missing values

We anticipate that some patients or their relatives may withdraw from the study until the end of the hospital stay. We are accounting for this dropout during patient recruitment. Moreover, we will report frequency and possible reasons for any missing data. For secondary endpoints, we do expect missing data due to patient dropout in the follow-up telephone call and will report frequency and possible reasons accordingly. In the health economic analysis, missing values may be imputed based on the final dataset. The specific imputation method will be detailed separately in the Health Economic Analysis Plan (HEAP).

#### Health economic evaluation

Analytical details will be provided in the HEAP, which will also be finalised until project month 30. Health economic analyses involving costs are necessarily country specific. We will establish resource use and cost implications, and cost-effectiveness (economic efficiency), of the intervention from the healthcare system, societal and institutional (centre) perspectives, for Germany and at least one other country (ideally, all other countries depending on local interest and support with the identification of unit cost data). As the standard cost-effectiveness metric (costs per quality-adjusted life year (QALY) gained) is potentially challenging to interpret in PC situations, the cost results will also be related to other trial outcomes in a cost–consequence analysis. The costs of the intervention will be estimated and considered at the patient-level economic analyses on a pro rata basis.

Analyses will follow the principles applied for the primary endpoint and clinical analyses, to the extent they are applicable. Cost will be calculated by combining resource use and informal care data with suitable unit costs or will be directly provided by the administrations of participating centres. QALYs will be calculated from utilities (derived from European Quality of Life-5 Dimensions 5-Level (EQ-5D-5L) Questionnaire responses by applying published algorithms) using standard area under the curve methods following the trapezium rule.^36^ Costs, QALYs and additional outcome parameters that may be of interest for the cost–consequence analysis part will initially be described using standard methods. The presence of international variation/heterogeneity will be explored. Incremental costs and effects will then be assessed using suitable statistical models, typically GLMMs^23^ considering the specific requirements of the stepped-wedge design and the distributional characteristics of the studied parameters (eg, expected right-skewed distributions of resource use and cost parameters). Alternative analytical methods will be performed as robustness checks. For example, in order to capture the potential correlation of incremental costs and effects, the use of Generalized Structural Equation Models^37^ in the stepped-wedge setting will be explored. Depending on the amount of missing values, multiple imputations may be applied. We will perform rigorous uncertainty analyses combining non-parametric bootstrap-based estimation of uncertainty ranges and probabilistic sensitivity analysis of parameters affected by second order uncertainty (eg, unit costs).

### Ethics and dissemination

#### Research ethics approval

This study is conducted in accordance with ethical principles that have their origin in the Declaration of Helsinki and are consistent with Good Clinical Practice and EU General Data Protection Regulation. The protocol is based on the underlying project application to the European Union HORIZON Europe programme, which received previous independent peer review as part of the grant funding process. Together with the patient information sheets and consent forms, the protocol was first approved by the ethics committee of the Charité-Universitätsmedizin Berlin and subsequently by all participating centres’ ethics committees (table 9). The study is registered in ClinicalTrials.gov (NCT06605079).

**Table 9 T9:** Ethics committees’ names and approval numbers

Country	Name of the ethics committee	Approval number
Germany	Charité’s Ethics Committee (Ethik-Kommission der Charité—Universitätsmedizin Berlin)	EA2/291/23
	Ethics committee at the medical faculty of Heinrich Heine University Düsseldorf (Ethikkommission an der Medizinischen Fakultät der Heinrich-Heine-Universität Düsseldorf)	2024-2823
	Ethics committee at Martin-Luther-Universität Halle-Wittenberg (Ethik-Kommission der Martin-Luther-Universität Halle-Wittenberg)	2024-063
Italy	Regional ethics committee of Umbria (Comitato Etico Regionale dell’Umbria)	4696/24
Czech Republic	Ethics committee of the General University Hospital in Prague (Etické komisi všeobecná fakultní nemocnice v Praze)	74/24 S Grant
Israel	Hadassah Medical Organization Institutional Review Board (ועדת הלסינקי להערכה מוסדית)	HMO-0062-24
Greece	National and Kapodistrian University of Athens Research Ethics Committee (Επιτροπή Ηθικής και Δεοντολογίας της Έρευνας (Ε.Η.Δ.Ε.) του Εθνικού και Καποδιστριακού Πανεπιστημίου Αθηνών)	125/2024
	Elena Venizelou—Alexandra General Hospital of Athens—Scientific Council (Γενικό Νοσοκομείο Αθηνών «Έλενα Βενιζέλου»—Αλεξάνδρα—Επιστημονικό Συμβούλιο)	99/22-02-2024
	Scientific council of the General University Hospital of Alexandroupolis (Πανεπιστημιακό Γενικό Νοσοκομείο Αλεξανδρούπολης—Επιστημονικό Συμβούλιο)	6851/05-02-2924
	General Hospital of Athens Evaggelismos-Polyclinic—Scientific Council—Ethics Committee («Γενικό νοσοκομείο Αθηνών Ευαγγελισμός—Πολυκλινική» Επιστημονικό Συμβούλιο—Επιτροπή Ηθικής και Δεοντολογίας)	320/19-06-2024
